### Secondary outcomes

By using repeated measures mixed models analyses the course of the secondary outcome(s) over time of both interventions will be compared. The following time points will be used, baseline and follow-up measurements at 6 weeks, 3, 6, 9, 12 months.

Change in secondary outcomes will be used as dependent variable. As secondary outcomes will be used: KOOS-PS/HOOS-PS; OKS/OHS, NRS, AAQ, EuroQol-5D-5L, performance-based test and the anchor and satisfaction questions.

#### Economic evaluation

The economic evaluation will consist of a cost-utility analysis from a societal perspective (costs per QALY), based on patient reports and with an undiscounted one-year time horizon. Average costs and outcomes will be statistically compared using net-benefit analysis, with multiple imputation to account for missing data. Quality-adjusted life years (QALYs) will be estimated using the Dutch tariff for the quarterly EQ-5D-5L measurements. Societal costs will include healthcare costs, patient and family costs, and productivity costs. The timing, contents, frequency and duration of PPT will be measured using the study registrations. Other healthcare use and productivity will be reported by patients using quarterly questionnaires (including general practitioner visits, outpatient visits, hospital days, medication, home and informal care, patient costs, absence from work, and productivity while at (unpaid) work). Healthcare will be valued using reference prices obtained from the Dutch guidelines for economic evaluations in healthcare, including time and travel costs. Sensitivity analysis will be performed on the cost perspective (healthcare instead of societal perspective), the valuation of productivity (human capital instead of friction cost approach) and the utility measure used to calculate QALYs (Visual analogue scale for health (with power transformation) instead of Dutch EQ-5D-5L tariff).

In addition to the CUA, a budget impact analysis (BIA) will be performed. In a cost-calculator spreadsheet model, budget impact will be evaluated from the perspectives of the Dutch ‘Budgettair Kader Zorg’ (BKZ), health insurers, and the different care providers. The analysis will take into account the current mix of treatments, with prices appropriate for the perspective, a 4-year time-horizon and different scenarios for the rate of uptake.

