## Trial objectives

The aim of the present study is to evaluate the (cost-) effectiveness of a standardized, treat-to-target PPT strategy in TKA and THA patients compared to usual PPT. We hypothesize that with the standardized treat-to-target strategy better functional outcome can be achieved compared to usual care with lower costs (superiority study). The results of this study will be used to develop and implement a nationwide treatment strategy for PT after TKA/THA, and will be integrated in national guidelines of PTs and orthopedic surgeons.

Primary objective
To assess whether the functional outcome of a standardized, personalized treat-to-target PT strategy after TKA and THA is superior to usual care PPT after 3 months follow-up.To assess whether a standardized, personalized treat-to-target PPT strategy is more cost-effective compared to usual care PPT after 12 months follow-up.

Secondary objective
To assess whether the functional outcome of a standardized, personalized treat-to-target PPT strategy after TKA and THA is superior to usual care PPT during the follow-up of 12 months.To assess the difference in function, performance-based tests, pain and quality of life, as well as anchor questions, and satisfaction question; between both groups over time (6 weeks, 3,6,9 and 12 months) during the first year.

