### Assessments

Patients will be asked to fill in questionnaires at baseline, and at 6 weeks, 3- (primary end-point), 6-, 9 and 12-months follow-up. Performance-based tests will be performed at baseline, 6- and 12 months (see Table 1 for an overview). In each participating hospitals an assessor will be trained by the coordinating researcher to perform these Performance-based tests.

**Table 1 Tab1:** Overview of measurement PATIO study

Timepoint	Allocation	Enrolment	Post-allocation	Close-out
	Randomization	Baseline, at inclusion	6 weeks,3, 6, 9 –months follow-up	12-months follow-up
Enrolment				
Eligibility screen		X		
Informed consent		X		
Allocation	X			
Interventions				
*Intervention group: Treat to target*			X	X
*Control group:* *Usual care*			X	X
ASSESSMENTS:				
*Demographic;* age, gender, side affected, BMI, education level, comorbidity		X		
*HOOS-PS / KOOS - PS*		X	X	X
*OHS / OKS*		X	X	X
*NRS*		X	X	X
*AAQ*		X	X (only at 3 months)	X
*EQ 5-D5L*		X	X	X
*Satisfaction question*			X	X
Cost-effectiveness			X	X
*Performance-based tests*		X	X (only at 3 months)	X
*(Serious) Adverse events*			X	X

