### Secondary outcomes

We also assessed the needed numbers to detect superiority of the treat-to-target PPT intervention to usual PPT for the outcome improvement of pain severity as assessed by the NRS. Based on a MCID of 1 point on the NRS, and a SD of 2 the needed numbers were assessed. Sample sizes of 117 in group one and 117 in group two, which were obtained by sampling 9 clusters with an average of 13 subjects each in group one (234 patients) and 9 clusters with an average of 13 subjects each in group two (234 patients), achieve 91% power to detect a difference between the group means of at least 1. The SD of subjects is 1.7. The intracluster correlation coefficient is 0.06. The coefficient of variation of cluster sizes is 0.500. A two-sided t-test was used with a significance level of 0.05. This test used degrees of freedom based on the number of subjects. To account for a 25% of dropout,624 patients will be needed of which 312 TKA and 312 THA patients.

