### Primary outcome measure

The difference between both groups in change of KOOS-PS/HOOS-PS between baseline and 3 months follow-up score will be used as primary outcome. Patients will be analyzed as treated.

The primary analyses will be performed by using mixed models (change in KOOS-PS/HOOS-PS during 3 months as dependent and intervention as independent variable). Change between baseline and 3 months follow-up score will be used as primary outcome. Hospital variable will be used to indicate the correlation structure in the model. Adjustments will take place for baseline values of KOOS-PS/HOOS-PS. Of variables of which a priori is known that they are associated with the change in KOOS/HOOS-PS, based on previous studies or based on a strong clinical rationale will be considered as covariates in the primary analysis. These covariates are age, gender, BMI, and surgical approach in THA (anterior, lateral and postero-lateral). The assumptions of constant variance and linear relationships will be assessed. Should any of these assumptions seriously fail then transformation of the dependent or independent variable(s) (where applicable) will be used. The choice of which transformation (e.g. square root, logarithm) will be used will be based on the specific distribution of the residuals.

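### The QALY is tied to quarterly EQ-5D-5L values, which leaves the scheduled 6-week measurement out of the 12-month cost-utility result

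*Protocol article*

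**What the plan says.** The Economic evaluation section plans a cost-utility analysis "based on patient reports and with an undiscounted one-year time horizon". On utilities it says: "Quality-adjusted life years (QALYs) will be estimated using the Dutch tariff for the quarterly EQ-5D-5L measurements". It gives no interpolation rule and does not say whether the baseline value enters the QALY.

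The measurement schedule is wider than quarterly. The Assessments section reads: "Patients will be asked to fill in questionnaires at baseline, and at 6 weeks, 3- (primary end-point), 6-, 9 and 12-months follow-up". In Table 1 the EQ-5D-5L row is marked at baseline, in the shared column for 6 weeks and 3, 6 and 9 months, and at 12 months. It lacks the restriction to 3 months that the AAQ and performance-test rows carry. The Secondary outcomes part of the Statistical analysis includes the EuroQol-5D-5L among its outcomes and states: "The following time points will be used, baseline and follow-up measurements at 6 weeks, 3, 6, 9, 12 months".

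Cost-effectiveness is listed under the primary objective: "To assess whether a standardized, personalized treat-to-target PPT strategy is more cost-effective compared to usual care PPT after 12 months follow-up".

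**The concern.** The article describes one instrument on two schedules: six time points for collection and for the repeated-measures analysis, and quarterly values for the QALY. The value that falls between the two is the 6-week one.

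Its position matters in this trial. In the intervention arm, physiotherapy starts with an assessment within 3 days of discharge and ends when the functional milestones are reached. Any difference between the strategies should therefore show early. A QALY built on baseline and quarterly values joins the pre-operative state to the 3-month state by a single straight line, across surgery and early rehabilitation. If one strategy brings patients back faster but the arms are close again by 3 months, that line cannot show it. At stake is how much of an early utility difference reaches the incremental QALY, and through it the net benefit.

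**Working it through.** The article states no utility, QALY or net-benefit figure, so there is nothing of its own to reproduce. The check has two parts.

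**1. What does quarterly mean here?** The same paragraph uses the word again for the questionnaires on healthcare use and productivity. The section on direct and indirect costs places those at 3, 6, 9 and 12 months, without 6 weeks. The natural reading is that the word means the same schedule both times. The three planned sensitivity analyses change the cost perspective, the valuation of productivity and the utility measure; none changes the EQ-5D-5L time points.

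**2. How much does leaving out 6 weeks change?** Assumptions: linear interpolation, baseline included, and months placed at weeks 0, 13, 26, 39 and 52. Each measurement's trapezoid weight in years is half the distance between its neighbours, divided by 52.

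| Time | Weight with 6 weeks | Weight without |
|---|---|---|
| Baseline | 3/52 = 0.058 | 6.5/52 = 0.125 |
| 6 weeks | 6.5/52 = 0.125 | not used |
| 3 months | 10/52 = 0.192 | 13/52 = 0.25 |
| 6 months | 0.25 | 0.25 |
| 9 months | 0.25 | 0.25 |
| 12 months | 0.125 | 0.125 |

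Let d0, d6 and d13 be the between-arm utility differences at baseline, 6 weeks and 13 weeks. At 6 weeks, the line from baseline to 3 months has the value (7/13)·d0 + (6/13)·d13. Subtracting the second set of weights from the first gives

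amount left out = 0.125 × [d6 − (7/13)·d0 − (6/13)·d13].

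This is the area of a triangle with base 0.25 year: 0.5 × 0.25 = 0.125.

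Results with d0 = 0 and no difference from 6 months on (all differences assumed):

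| d6 | d13 | QALY with 6 weeks | QALY without | Left out |
|---|---|---|---|---|
| 0.02 | 0 | 0.0025 | 0 | 0.0025 |
| 0.05 | 0 | 0.0063 | 0 | 0.0063 |
| 0.10 | 0 | 0.0125 | 0 | 0.0125 |
| 0.05 | 0.025 | 0.0111 | 0.0063 | 0.0048 |
| 0.10 | 0.05 | 0.0221 | 0.0125 | 0.0096 |
| 0.05 | 0.05 | 0.0159 | 0.0125 | 0.0034 |
| 0.05 | 0.08 | 0.0216 | 0.0200 | 0.0016 |
| 0.0231 | 0.05 | 0.0125 | 0.0125 | 0 |
| 0 | 0.05 | 0.0096 | 0.0125 | −0.0029 |

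Fourth row in full: with 6 weeks, 0.125 × 0.05 + 0.1923 × 0.025 = 0.0111; without, 0.25 × 0.025 = 0.0063. The 0.0048 left out is about 43% of the gain in that scenario. The last two rows mark the limits. If the difference grows linearly to 3 months (6/13 × 0.05 = 0.0231), nothing is lost. If it appears only after 6 weeks, the quarterly version overstates it.

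In money, at an assumed EUR 20,000 to 80,000 per QALY, 0.0025 QALY is EUR 50 to 200 per patient and 0.0125 QALY is EUR 250 to 1,000.

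**The case against.** The best defence is that quarterly is shorthand for the follow-up schedule and that the 6-week value was never meant to be excluded. The article does not say that it is discarded, and it is not lost to the trial, because the secondary analysis uses it. Nor does the section say that baseline is kept or that interpolation is linear, so the arithmetic above depends on a reading. This is fair, and it limits how firmly the point can be put. But the same word in the same paragraph describes a schedule that has no 6-week point, so the defence needs the word to carry two meanings.

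It can also be said that the 6-week EQ-5D-5L is inferred from general statements. Table 1 groups 6 weeks with later visits, and the list of secondary time points also covers outcomes not measured at 6 weeks. That is true, but nothing in the article restricts the EQ-5D-5L to fewer times, whereas such restrictions are written out for other instruments.

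The third objection is size. The 3-month value, which is the chosen primary time point, is retained. Interpolating across surgery affects both arms, so only a between-arm departure from the line counts. Every utility difference used here is assumed. All of this stands: the absolute loss is small and may be zero.

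A reader might go further and infer that the net-benefit comparison is unadjusted for baseline utility, ignores hospital, or imputes without hospital. The text says only: "Average costs and outcomes will be statistically compared using net-benefit analysis, with multiple imputation to account for missing data". It names no covariates and excludes none. The clinical model does state its adjustment ("Adjustments will take place for baseline values of KOOS-PS/HOOS-PS") and uses hospital for its correlation structure, but that contrast does not show that the economic analysis omits either. A condensed article commonly leaves such detail to the full plan, so none of this is a finding.

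**Conclusion.** The point holds in a limited form. As written, the QALY definition does not match the EQ-5D-5L schedule given elsewhere in the article. It leaves out the only utility value between the pre-operative baseline and 3 months.

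The usual consequence, if a benefit appears early and fades, is that part of it is kept out of the cost-utility result. Under linear interpolation from baseline, the amount is about 0.0025 to 0.0125 QALY for assumed 6-week-only differences of 0.02 to 0.10, and zero under linear divergence to 3 months. It can be a sizeable share of a small incremental QALY, as in the scenario with 0.0111 against 0.0063. The article gives no expected incremental QALY or cost, so it cannot be shown that the omission would change the sign of the net benefit, tempting as that inference is.

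The change is worth making because cost-effectiveness stands under the primary objective and the correction is almost free.

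**What to change.** Replace the QALY sentence in the Economic evaluation section with one stating that each patient's QALY is the area under the utility curve, by linear interpolation, over all six scheduled EQ-5D-5L measurements: baseline, 6 weeks, and 3, 6, 9 and 12 months, valued with the Dutch tariff. A version using baseline and the quarterly values only can be kept as a sensitivity analysis, which would show directly how much the 6-week value contributes. If the 6-week EQ-5D-5L is in fact not collected, correct Table 1 and the secondary-outcome time points instead.

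The cost is a change of wording and one extra run of the analysis. The schedule already provides the data, so no visit, questionnaire or patient is added. The article reports that inclusion was still ongoing, so the definition could be fixed before the analysis.

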## Discussion

The PATIO trial is, to our knowledge, the first study that analyses the (cost-)effectiveness of a standardized, personalized postoperative physiotherapy protocol compared to usual postoperative care in patients with OA receiving TKA/THA.

Given the large variation in the provision of PPT, which seems to be not or weakly associated with patient characteristics, a more standardized, personalized approach seems warranted. The planned randomized controlled trial, with an economic evaluation will answer the question whether patients who receive a treat-to-target intervention recover with better functional outcomes against lower costs compared to the usual care PPT. From the health care and societal perspective it is extremely relevant that the most optimal PPT treatment strategy is used, as it concerns about 1.66 (THA) and 1.26 (TKA) per 1.000 people per year in western countries [16].

Besides measuring the (cost-) effectiveness of a treat-to-target PPT we also asses a broader range of health aspects (e.g. physical function, pain, comorbidities, perceived health and mental factors, information on insurance and satisfaction level of the results of their surgery and the PT) because several factors can influence the individual recovery after TKA/THA.

Strengths of the study include the nationwide multicenter design, supported by multiple involved professions. PTs are trained to work with the treat-to-target protocol. PTs who are trained on the protocol will unconsciously adapt their usual care treatment. To avoid contamination between the treat-to-target PPT and the usual care PPT a cluster RCT design was chosen. When a PT is trained by the treat-to-target protocol he/she will only treat patients in the intervention group. Since the power and precision of a cluster randomized trial is lower than an individually randomized trial, our study needs more participants to obtain the same statistical power. Another possible limitation of the study is the variation in surgical techniques which may have a different effect in the first months of the revalidation period of the patient.

The results of this study will address an important evidence gap and will have significant impact on the daily practice of the physiotherapist.

## Trial status

The study inclusion has started in August 2018 and is still ongoing.

## Data Availability

The datasets used and/or analyzed during the current study are available from the corresponding author on reasonable request.

## Abbreviations

PTT: Postoperative physical therapy
PT: Physical therapy
PTs: Physical therapist
OA: Osteoarthritis
TKA: Total knee arthroplasty
THA: Total hip arthroplasty
NOV: Dutch Orthopaedic Association
KNGF: the Royal Dutch Society for Physical Therapy
BMI: Body mass index
KOOS: Knee injury and osteoarthritis outcome score
HOOS: Knee disability and osteoarthritis outcome score
OKS: Oxford knee score
OHS: Oxford hip score
NRS: Numeric rating scale (NRS)
NZa: The Dutch Healthcare Authority
BKZ: Dutch Budgettair Kader Zorg
Qaly: Quality adjusted life year
OARSI: Osteoarthritis Research Society International
